## Abstract

**Background:**

During the last decade, the use of ministernotomy in cardiac surgery has increased. Quality of life and patient satisfaction after ministernotomy have never been compared to conventional full sternotomy in randomised trials. The aim of the study is to determine if this minimally invasive approach improves quality of life, satisfaction and clinical morbimortality outcomes.

**Methods/design:**

The QUALITY-AVR trial is a single-blind, single-centre, independent, and pragmatic randomised clinical trial comparing ministernotomy (“J” shaped upper hemisternotomy toward right 4th intercostal space) to full sternotomy in patients with isolated severe aortic stenosis scheduled for elective aortic valve replacement. One hundred patients will be randomised in a 1:1 computational fashion. Sample size was determined for the primary end point with alpha error of 0.05 and with power of 90% in detecting differences between intervention groups of ≥ 0.10 points in change from baseline quality of life Questionnaire EuroQOL-index (EQ-5D-5 L®), measured at 1, 6 or 12 months. Secondary endpoints are: the differences in change from other baseline EQ-5D-5 L® utilities (visual analogue scale, Health Index and Severity Index), cardiac surgery specific satisfaction questionnaire (SATISCORE®), a combined safety endpoint of four major adverse complications at 1 month (all-cause mortality, acute myocardial infarction, neurologic events and acute renal failure), bleeding through drains within the first 24 h, intubation time, postoperative hospital and intensive care unit length of stay, transfusion needs during the first 72 h and 1-year survival rates. Clinical follow up is scheduled at baseline, 1, 6, and 12 months after randomization. All clinical outcomes are recorded following the *Valve Academic Research Consortium 2 criteria.*

**Discussion:**

The QUALITY-AVR trial aims to test the hypothesis that ministernotomy improves quality of life, satisfaction and clinical outcomes in patients referred for isolated aortic valve replacement. Statistically significant differences favouring ministernotomy could modify the surgical “gold standard” for aortic stenosis surgery, and subsequently the need to change the control group in transcatheter aortic valve implantation trials. Recruitment started on 18 March 2016. In November 2017, 75 patients were enrolled.

**Trial registration:**

ClinicalTrials.gov, NCT02726087. Registered on 13 March 2016.

**Electronic supplementary material:**

The online version of this article (10.1186/s13063-018-2486-x) contains supplementary material, which is available to authorized users.

## Background

The progressive ageing of the population has caused an increase in aortic valve procedures due to degenerative diseases [1], while mortality has decreased thanks to improvements in surgical techniques [2]. The current “gold standard” is conventional surgery with a full median sternotomy (FS) to replace the aortic valve. In the last decade, to minimise invasiveness and improve outcomes, there has been an increase in the use of smaller incisions such as the ministernotomy (MS) and new technologies (transcatheter aortic valve implantation (*TAVI*), or sutureless valves).

Minimally invasive aortic valve replacement (AVR) surgery was first described in 1993 [3] and popularised between 1996 and 1997 [4] as an alternative to FS for patients with isolated aortic valve or ascending aorta pathologic conditions. Various techniques have been described, although currently the most frequently used is MS (partial upper hemisternotomy extended in a J-shape into the right fourth intercostal space, Fig. 1) [5]. In 2008, the American Heart Association defined minimally invasive surgery as “a small chest wall incision that does not include the conventional FS” [6].

**Fig. 1 Fig1:**
[figure not shown]
Ministernotomy extended in a J-shape into the right fourth intercostal space. **a** Before sawing. **b** Surgical view after sawing, retraction and cannulation

To date, few clinical trials have been conducted that compare AVR surgery using MS versus FS [7–11]. No significant differences have ever been found, due to inadequate design, lack of statistical power or too small a sample size for the primary endpoint of mortality, even though there have been significant differences in morbidity with MS (lower rates of pain, transfusions, bleeding, mechanical ventilation time, stay in intensive care and hospital, etc.) To detect differences in mortality with sufficient power, over 1100 patients would be needed for each branch of the study. This circumstance caused a spate of retrospective studies analysing propensity scores, and meta-analysis [12–14], which confirmed a reduction in postoperative morbidity, and demonstrated a decrease in early [13–15], and even in late, mortality [13]. But there is an evident bias inherent to retrospective studies. This increased the use of MS worldwide, above all as a result of the spread of TAVIs.

There have been no prospective studies to measure patient quality of life (QOL) and compare the techniques of MS versus FS for AVR. There has only been one retrospective study, with results that are not statistically significant [16]. Two clinical trials have compared TAVI versus FS (the PARTNER [17] and the Core Valve PIVOTAL trials [18]) but they did not analyse MS. QOL has always been relevant to the patient; however, clinicians have not given it enough relevant focus, and it is usually and statistically significant in the first month in favour of TAVI [17, 18], with all data coming from secondary analysis, not primary endpoints.

Patient-reported QOL outcomes were selected to be the primary endpoint because if similar recovery time and QOL to TAVI is demonstrated, MS provides the capacity of implantation of more durable valves; therefore, it would be used in patients at low and intermediate risk, given the unknown long-term durability of TAVI valves after 5 years. To date, however, there has been no specifically designed QOL study. For all of these reasons, we designed this clinical trial to compare the QOL after MS versus FS. Satisfaction with the surgery and morbimortality outcomes will also be measured.

## Methods/design

This randomised clinical trial follows the standard protocol items: recommendation for interventional trials (SPIRIT) guidelines (see Additional file 1). The study schedule of enrolment, interventions, and assessments is presented in Fig. 2.

**Fig. 2 Fig2:**
[figure not shown]
Standard protocol items: recommendation for interventional trials (SPIRIT) figure of participant timeline. EQ5D, Euroqol 5 dimensions Quality of life Questionnaire; M, month; NYHA, New York heart Association; OR, surgery in the operating room; PREOP, preoperative; VAS, visual analogue scale

### Study design and endpoints

This is a pragmatic [19], independent (not industry supported), single-blind (patient), single centre, randomised clinical trial that compares two treatment groups: patients undergoing AVR with FS or with MS. The study was approved by our Institution’s Ethics Committee for Research (Institutional Review Board), and was registered at ClinicalTrials.gov
**(NCT02726087**) before the first patient was randomised on 18 March. At January 2018, current protocol version is 1.4 after minor changes were performed.

### Quality of life and satisfaction questionnaires

The outcome of heart surgery may be evaluated by means of “hard” outcomes, such as mortality, survival, morbidity and heart function, or at different points in time, but the impact of the operation is not merely limited to these biological aspects. An adequate assessment should cover other areas, such as psychological and social aspects, which requires the use of psychometric tools, such as questionnaires. Within these areas, one of the most important is assessment of patient QOL, whereby questionnaires are used to explore physical, psychological and emotional aspects.

There are a multitude of questionnaires including the Short Form 36-item Health Survey [20], the Minnesota Living with Heart Failure (MLWHF) [21], the Short Form 12 [22], the Kansas City Cardiomyopathy Questionnaire (KCCQ) [23], and the EuroQoL 5 Dimensions 5 Levels (EQ-5D-5 L®) [24]. We chose the latter as it had been tested in the Spanish population in the Spanish National Health Survey 2011–2012. It was validated for cardiovascular pathologies and it can measure a health unit, the quality-adjusted life year (QALY).

**The EQ-5D-5 L® questionnaire** presents various utilities to measure QOL. The main ones are a descriptive system that can be used to calculate an EQ-index and the visual analogue scale (**VAS**); other utilities may also be calculated such as the severity index or the health index. This questionnaire estimates the state of health in 5 dimensions (mobility, self-care, usual activities, pain/discomfort and anxiety/depression), with five possible responses depending on extent (5 levels: no problems, slight problems, moderate problems, severe problems, unable to /extreme problems). The **EQ-5D-5 L® index** is calculated via the application, the EQ-5D-5 L® Crosswalk Index Value Calculator, using a logistic regression model. Thus, EQ-5D-5 L® (5 dimensions on 5 levels) distinguishes 3125 states of health. The index takes values between 1 (state of health 11111) and − 0.654 (state of health 55555) in the Spanish population.

The subjective state of health is estimated using the VAS of 0 to 100, where 0 is the worst imaginable health and 100 is the best imaginable health.

The **Severity Index (SI)** is obtained by adding the digits that correspond to the levels of the 5 dimensions in each state of health, subtracting 5 and multiplying by 5, which produces a new index (0–100), where 0 indicates a total absence of health problems and 100 is the highest degree of severity. Subtracting the SI from 100 will give the **Health Index (HI).**

As soon as the patient has signed the consent form, the baseline preoperative questionnaires will be completed, which will be repeated at 1, 6 and 12-month follow up. All questionnaires can be completed in person or by telephone interview.

**The SATISCORE® questionnaire** [25] assesses patient satisfaction after undergoing heart surgery. It analyses six dimensions of satisfaction with the surgery: vitality, sociability, mood, sexuality, self-perception and rest. It consists of twenty statements (Table 1) with 6 possible responses on a Likert scale: 0, no answer; 1, very unsatisfied; 2, unsatisfied; 3, don’t know; 4, satisfied; and 5, very satisfied. Scores range from 0 to 100 and it is valid specifically to evaluate the satisfaction of patients who have undergone heart surgery. It is completed at 1 month and 6 months post-surgery.

**Table 1 Tab1:** Items included in the SATISCORE® questionnaire

Feeling of illness	
Pain	
Feeling of fatigue	
Feeling when you get up in the morning	
Exercise you have been indicated	
Pharmacological treatment	
Feeling about the operation	
Feeling of tiredness	
Your state of health	
Perception of future health	
Attitude to your illness	
The life you lead today	
Feeling about the operation	
Family relationships	
Friendships	
Medical assistance received in the hospital	
Willingness to repeat the operation	
Future plans	
Sex life	
Precaution in sexual relations due to the operation	

### Selection of patients, randomisation and follow up

The study will recruit patients over the age of 18 years, who have severe aortic stenosis or double aortic lesion with predominant stenosis, who are symptomatic according to current guidelines [26] and also meet the inclusion and exclusion criteria (Table 2). All patients will receive oral and written information from a staff surgeon about the study and then as an informed patient sign a consent form before their inclusion and randomisation in the study. These data were recorded in the hospital computerized healthcare database.

**Table 2 Tab2:** Inclusion and exclusion criteria

Inclusion criteria
• Severe aortic stenosis (calcified aortic valve, aortic valve area < 1 cm^2^ or body surface area index < 0.6 cm^2^, mean transvalvular gradient > 40 mmHg or peak systolic velocity > 4 m/s) or double aortic lesion with predominance of stenosis
• Sympotomatic (dyspnea NYHA score ≥ 2, angina or syncope)
• Age ≥ 18 years
• Capacity to give informed consent
Exclusion criteria
• Moderately depressed ejection fraction (< 40%)
• Prior heart surgery (redo operation)
• Emergent surgery (within the first 24 h of admission)
• Infectious endocarditis
• Chronic obstructive pulmonary disease greater than moderate (forced expiratory volume at 1 s (FEV1) predicted < 60% measured by spirometry)
• Need for concomitant surgery except Morrow myectomy preoperative or intraoperative

Randomisation is performed using a randomisation computer programme, in blocks of four patients in a ratio of 1:1. Allocation concealment is achieved by an administrative officer who maintains custody of the randomisation sequence (sequentially numbered), and communicates to medical staff the treatment assigned. This is performed after the consent form has been signed and the surgery scheduled. The patient is blinded with respect to the treatment received. All wounds will be covered up to this moment with standardised wound dressings. There is great difficulty in blinding surgical procedures for a long time, because incisions and scars may differ between groups [27]. That is why the size of the wounds in both arms will be intended to be as small as possible, about 10 cm in the ministernotomy and 13–15 cm in conventional surgery. A standardized hospital discharge report will be used, without breaking the blinding unless it is strictly necessary due to medical needs, up to the final follow-up assessment at 1 year post-surgery. With these measures we will try to reduce the risk of bias, which will always be present in this type of study involving surgical procedures (for example with a surgeon who is not blinded to procedure). The outcome assessor is the Hospital Clinical Trials Data Monitoring Unit, independent from the Sponsor, which reviews and confirms all the outcomes and endpoint values every 3 months. Both groups of patients will receive clinical follow up and complete the EQ-5D-5 L® quality of life questionnaire at 1, 6 and 12 months, and the SATISCORE® at 1 and 6 months.

Any changes to the research protocol will be reviewed by the Institutional Review Board (IRB). Amendments will be made to the trial registry as necessary.

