### Sample size calculation

A review of previous work [28, 29] shows that the standard deviations of the EQ-5D-5 L® index in cardiovascular disease varies between 0.10 and 0.22, while VAS score varies between 8 and 21 depending on the severity. Likewise, in the only (multicentre) study [17] that determines quality of life in aortic stenosis, the standard deviation for high-risk patients scheduled for AVR was 0.17 in patients randomised to FS versus TAVI. For these reasons, on summary of all previous work, we used a standard deviation of 0.15 for the EQ-5D-5 L® index to calculate the sample size.

In QOL studies, it is not only important to ascertain whether there are significant differences, but also to know if these differences are clinically relevant. This is why the concept of the **minimal important difference (MID)** was created, which in previous research among patients with cancer was 0.08 points on the EQ-5D index and 7–11 points on the VAS [29], and in patients with stroke it was 0.10 points on the EQ-index (95% CI 0.08–0.12) [28]. This difference was also 0.06 points (95% CI 0.02–0.10) on the EQ index during the first month in the PARTNER 1 study (transfemoral TAVI versus FS) [17], and 0.12 (95% CI 0.08–0.16) in the CoreValve PIVOTAL trial study [18]. As there was no existing specific calculation of MID for cardiology patients with severe aortic stenosis, we arbitrarily established the interval of 0.10 points on the EQ-5D index (the mean value from previous studies) as the clinically relevant difference to detect. Thus, to detect an MID of at least 0.10 points in the QOL scale EQ-5D-5 L® index, with alpha error of 0.05, beta error of 0.1 and power of 90% for two-tailed contrast of two independent means (SD 0.15), two groups of 48 patients are necessary to provide a minimum of 96 patients. In view of possible losses to follow up, 100 patients will be randomised. If patients drop out or are excluded during the study, additional patients will be recruited until a minimum of 96 patients is achieved, and inclusion of an additional patient will be considered again for each patient not completing the 1-year follow-up assessment.

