Multivariate regression analysis techniques will be applied to control possible bias in effect caused by the patient’s initial situation (comorbidities). Pearson’s correlation test will be performed on EQ-5D-5 L® and SATISCORE® data. Survival analysis will be conducted using Mantel Cox log-rank analysis with the corresponding Kaplan-Meier survival chart.

The “intention to treat” population is defined to include all randomised subjects. This population will be used for endpoint analyses. The as-treated population (“per protocol”) is defined to include all subjects undergoing the index procedure. This population will be used for the analysis of adverse events.

Differences between MS and FS group scores at each follow-up time point will be estimated with longitudinal random-effect growth curve models, which will be fit to the repeated measurements for each health status outcome. These longitudinal analyses will use all available quality-of-life data: including data from patients who will subsequently die, withdraw, or will be lost to follow up. They will also accommodate missing data under the missing at random assumption. Variables that will be included in the models are: treatment assignment, pre-specified patient characteristics (age, sex, EuroScore), follow-up time and interactions between treatment and time. These models will be used to calculate the mean between-group differences in the EQ-5D index score and the individual subscales at each follow-up time point, and the associated 95% CIs and *P* values.

To examine the potential impact of missing data, which, given the illness severity of the trial population, would most likely not be missing at random, we will repeat the growth curve analyses after imputing the missing scores among the surviving patients, as the lowest reported score among respondents within each treatment group for each respective time point. We also will examine the magnitude of potential survivor bias by comparing the mean baseline scores between treatment groups for the subgroups of patients with available QOL data at each successive follow-up time point.

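### Exclusion of patients after randomisation, possibly for a need for concomitant surgery found in theatre, cannot be reconciled with an intention-to-treat population of all randomised subjects

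*Protocol article*

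**What the plan says.** Four parts of the protocol article bear on this.

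- **Timing and knowledge of allocation** (Selection of patients, randomisation and follow up). Of the assignment step the text says "This is performed after the consent form has been signed and the surgery scheduled", so it precedes the operation. The officer who holds the sequence "communicates to medical staff the treatment assigned", and the section concedes a risk of bias "with a surgeon who is not blinded to procedure".
- **Eligibility** (Table 2, same section). One exclusion criterion reads "Need for concomitant surgery except Morrow myectomy preoperative or intraoperative".
- **Replacement** (Sample size calculation). The general rule is "If patients drop out or are excluded during the study, additional patients will be recruited until a minimum of 96 patients is achieved". A second, softer provision covers patients who miss the last visit: a further recruit may be taken on for each of them.
- **Analysis set** (Statistical analysis). The intention-to-treat "population is defined to include all randomised subjects" and serves the endpoint analyses. The as-treated set, made up of those who undergo the index procedure, is reserved for adverse events.

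The article does not say whether a randomised patient who is later excluded stays in follow-up and in the intention-to-treat analysis.

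**The concern.** An exclusion criterion protects a randomised comparison only if it is settled before allocation. If a need for concomitant surgery that emerges in theatre counts as an exclusion, the decision falls after allocation and is taken by someone who knows the arm. Patients removed in this way need not be alike in the two arms, and the remaining groups are then no longer the groups that randomisation formed.

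The sample size section makes this more than a stray phrase in a table. It treats exclusion during the study as an expected event and recruits until the count is restored, which suggests that excluded patients do not count towards the 96. One team could follow Table 2 and the sample size section and drop these patients. Another could follow the statistical section and keep them. Both would be working from the same protocol, yet they could report different primary results. If excluded patients are not followed, their outcomes cannot be recovered later.

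**Working it through.** **1. The plan's own figure.** Inputs from Sample size calculation: difference 0.10, SD 0.15, two-sided alpha 0.05, power 90%.

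n per arm = 2 × [SD × (z for 0.975 + z for 0.90) / difference]² = 2 × [0.15 × (1.960 + 1.282) / 0.10]² = 47.28, rounded up to 48, so 96 in total.

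The stated 48 per arm reproduces under the normal approximation and is not in dispute. Randomising 100 implies an allowance of 1 − 96/100 = 4%.

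**2. The passages side by side.**

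| Question | Table 2 and Sample size calculation | Statistical analysis |
|---|---|---|
| Can a randomised patient be excluded? | Yes, during the study; on one reading, for a finding in theatre | No: all randomised subjects are in the set |
| Does that patient count? | Apparently not: others are recruited to reach 96 | Yes, for endpoint analyses |

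The statistical section says that the longitudinal models use data from patients who die, withdraw or are lost. Excluded patients are not on that list, so the conflict is not resolved there.

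**3. How much exclusion could matter.** The article gives no exclusion rate and no outcome for such patients, so what follows is illustration under assumed values. Take an arm of 50. Let k patients be excluded, with a mean change in EQ-5D index worse by D than the mean r of those retained.

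Mean of the whole arm = [(50 − k) × r + k × (r − D)] / 50 = r − (k/50) × D.

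Exclusion therefore shifts the arm mean by (k/50) × D:

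| k excluded | D = 0.10 | D = 0.20 | D = 0.30 |
|---|---|---|---|
| 1 | 0.002 | 0.004 | 0.006 |
| 2 | 0.004 | 0.008 | 0.012 |
| 3 | 0.006 | 0.012 | 0.018 |
| 5 | 0.010 | 0.020 | 0.030 |

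Against the 0.10 target, the range is 0.002/0.10 = 2% to 0.030/0.10 = 30%. If both arms lose patients, the effect on the comparison is the difference between the two shifts, and it is zero when they are equal. Recruiting others like those retained restores the count but leaves the shift in place.

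**4. What happens to power without replacement.** With 100 randomised, power under the normal approximation is 90.4% at the implied 4% loss. At assumed losses of 5%, 10% and 15% it is 90.1%, 88.5% and 86.7%. To keep 96 evaluable at an assumed 10% loss, 96/0.90 = 106.7, so 107 would have to be randomised.

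**The case against.** The strongest reply concerns grammar. The words about timing in Table 2 come directly after the myectomy and may qualify that exception alone. On that reading, the table does not mention an exclusion in theatre. This is a fair reading and cannot be ruled out. It does not remove the conflict, because the sample size section still provides for exclusion during the study.

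Three stronger claims are tempting, and the reply to each of them stands.

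- *Replacement itself breaches intention to treat, or fills the trial with survivors.* The replacement clause governs recruitment, while the statistical section governs analysis. That section keeps data from patients who die, withdraw or are lost, and adds a low-score imputation and a survivor-bias check. Replacing dropouts is harmless to the analysis set if the first patients stay in it. For those who miss the 1-year assessment, an additional inclusion is only to be considered. The conflict comes from exclusion.
- *Replacing 1-year non-completers forces late, non-concurrent enrolment.* Recruitment began in March 2016 and was expected to end in May 2018. Patients operated on up to about May 2017 therefore reach 12 months within that window. Additional patients who enter "in blocks of four patients in a ratio of 1:1" would in any case be concurrent across the arms.
- *The surgeon selects who is analysed.* The text shows knowledge of the arm and an opportunity. It describes no mechanism by which the need for concomitant surgery would be judged differently by arm, and it apart from access describes the two operations as similar.

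It is also fair to say that a deficit of 0.30 is twice the planning SD (0.30/0.15 = 2) and that placing all exclusions in one arm is an extreme case.

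**Conclusion.** The point holds as an unresolved contradiction about who enters the primary comparison. The sample size section lets randomised patients be excluded and others recruited to make up the number; the statistical section analyses everyone randomised. Table 2 makes this worse on the reading in which a finding in theatre counts, since that judgement comes after allocation and is not blinded.

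The size of any bias is unknown, and it may be zero. The range of 0.002 to 0.030 rests wholly on the assumed numbers, the assumed deficits and the placing of all exclusions in one arm; its upper end is a high case. A reader might infer that exclusions depending on the arm have taken place, or that replacement alone invalidates the analysis. The article supports neither. The matter still deserves correction, because it concerns the composition of the analysis set and the change needed is short.

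**What to change.** Reconcile Table 2, Sample size calculation and Statistical analysis as follows.

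- **Table 2:** apply the concomitant-surgery criterion only to needs known before randomisation, and word the myectomy exception so that it has one reading.
- **Statistical analysis:** state that every randomised patient, including one found in theatre to need concomitant surgery, is followed up and analysed in the allocated arm. Any set that omits such patients serves only as a sensitivity analysis.
- **Sample size calculation:** strike the reference to exclusion. State that any additional recruits enter through the same 1:1 randomisation and add to the intention-to-treat set without replacing anyone in it.

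There is no need to cap the trial at 100, since extra randomised patients protect power if all are analysed. A larger number fixed in advance, such as 107 for an assumed 10% loss, would serve the same purpose.

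The cost is a short amendment and slight dilution of the contrast by patients with added procedures. Should the sponsor find that any randomised patient has already been excluded, that patient belongs in the intention-to-treat set; the article reports no such case.

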### Limitations of the study

Among this study’s limitations, there could be some confusion bias introduced by variables, which will be controlled in the statistical analysis using multivariate linear regression analysis. The absence of masking the surgeon may introduce an unmeasurable bias into the study. The sample size is not designed to detect differences in mortality, although a combined safety endpoint such as this one may help to find differences between groups. The use of general QOL questionnaires such as EQ-5D-5 L means that the outcome does not depend exclusively on the surgical technique employed, but also on other diseases and/or complaints that the patient has previously or that may be acquired in the future, independently of the heart condition. The size of the sample could also be insufficient if the standard deviations are shown to be higher than those presented in previous research.

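### One stated block size of four, in a single centre with unblinded surgeons, makes a third of allocations foreseeable to anyone who knows the size and tracks assignments

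*Protocol article*

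**What the plan says.** The section on selection, randomisation and follow up of the protocol article fixes the method: "Randomisation is performed using a randomisation computer programme, in blocks of four patients in a ratio of 1:1". It gives no second block size and mentions no strata.

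The study design section describes a "single-blind (patient), single centre, randomised clinical trial". On recruitment: "All patients will receive oral and written information from a staff surgeon about the study". On concealment: "Allocation concealment is achieved by an administrative officer who maintains custody of the randomisation sequence (sequentially numbered), and communicates to medical staff the treatment assigned". On timing: "This is performed after the consent form has been signed and the surgery scheduled". The same section gives, as an example of residual bias, "for example with a surgeon who is not blinded to procedure". The limitations section adds: "The absence of masking the surgeon may introduce an unmeasurable bias into the study".

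The sample size section plans 100 randomised patients and allows more to be added for those who drop out, are excluded or do not complete one year. The trial status section reports 75 recruited at November 2017, with recruitment expected to end in May 2018.

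**The concern.** Custody of the list stops anyone from reading the next line. It does not stop anyone from inferring that line. With one list in one centre, a single sequence unfolds in front of the team that recruits, because medical staff are told every assignment and the operation itself reveals the arm. If the block size is known to be four, part of each block can be worked out from what came before.

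A recruiter who expects a particular arm next can, without intending harm, choose whom to approach or when to enrol. Prognosis could then differ between arms. The primary endpoint is a self-reported score in about 100 patients with a target difference of 0.10. Adjustment for age, sex and EuroScore removes only the selection that those variables capture.

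**Working it through.** **The plan's own figures.** The article gives no figure for predictability. Its sample size reproduces: 2 × (1.960 + 1.282)² × 0.15² / 0.10² = 47.3, rounded up to 48 per group and 96 in total. This point does not affect it.

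**Inputs from the article.** Block size 4, ratio 1:1, one centre, 100 patients planned (25 blocks), 75 recruited at November 2017. *Assumption:* an observer knows the block size and all past assignments.

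**Certain allocations.** A 1:1 block of four has 6 orderings, hence 24 positions.
- The fourth position is always determined: 6 of 6.
- The third is determined when the first two are alike (AABB, BBAA): 2 of 6.
- Total: 8 of 24 = 33.3%, or 4/3 per block. Over 25 blocks this is 25 × 4/3 ≈ 33 patients.

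**Best guess (always name the arm that is behind).** Success by position is 1/2, 2/3, 2/3 and 1. The sum is 17/6 per block, and (17/6)/4 = 17/24 = 70.8%.

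**Alternatives.** Fixed sizes were enumerated. Varied sizes were simulated with 100 patients, each size equally likely, and an observer who knows the possible sizes and all past assignments.

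| Blocks | Certain | Best guess |
|---|---|---|
| Fixed 4 | 33.3% | 70.8% |
| Fixed 6 | 25.0% | 68.3% |
| Fixed 8 | 20.0% | 66.6% |
| Varied 4/6 | 5.6% | 69.2% |
| Varied 4/6/8 | 2.3% | 67.9% |

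Varying the size removes most of the certainty but little of the best-guess advantage. In the simulation, the simple rule of naming the arm that is behind, which needs only the running tally, also succeeded 67.9% of the time under 4/6/8.

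**What steering could do (illustration).** Let D be the difference in expected EQ-5D change between patients enrolled when ministernotomy is foreseen and those enrolled when full sternotomy is foreseen. The article gives no value for D.
- Acting only on certain allocations: bias = D/3.
- Acting on every best guess: bias = (0.708 − 0.292) × D = 0.417D.
- For D = 0.04 to 0.10, the bias runs from 0.04/3 = 0.013 to 0.417 × 0.10 = 0.042, or 13% to 42% of the 0.10 target.
- To create the whole 0.10, D must be 0.10/0.417 = 0.24 (1.6 planning SDs of 0.15) or 0.10 × 3 = 0.30 (2 SDs).

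**What a check on the first 75 could show.** About 75/3 = 25 allocations were forced, roughly 12 towards each arm. If baseline scores have an SD of 0.15 (an assumption that borrows the planning SD), the standard error of the difference is 0.15 × √(1/12 + 1/12) = 0.061. The 95% half-width is 1.96 × 0.061 = 0.12, so only a large imbalance would show.

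**The case against.** **Safeguards exist.** Allocation follows consent and scheduling, an administrative officer holds the list, and the eligibility criteria are largely objective. This stands in part. Declining or rescheduling a patient after an assignment is limited; choosing whom or when to enrol beforehand is not.

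**Foreseeability is conditional.** This stands. Nothing says that recruiters knew the block size or kept a tally. A reader might infer that a third of allocations were in fact known in advance, but the article supports only that they could be. Nor can publication have exposed the first 75 patients: the article describes the protocol as of January 2018, after they were enrolled. Operations may not follow allocation order either, so a tally of operations is an imperfect guide. The more direct route is that staff are told each assignment.

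**A single size is read from a condensed article.** This stands as a caveat. The full protocol might vary or conceal the size.

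**The gain over best guessing is small.** This stands. It is tempting to set 70.8% against 50%, but varied blocks do not deliver 50%. The gain is in certain allocations.

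**Large steering is needed to create the target effect.** Correct, at 1.6 to 2 SDs. Smaller steering could still bias the estimate. Change from baseline and covariate adjustment would absorb some of it, but only what is measured.

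**The limitations statement is no admission.** A reader might take it as conceding predictable allocation. It concerns the unmasked surgeon in general and does not mention block size.

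**Conclusion.** The point holds as an avoidable weakness in a stated design choice. Under blocks of four, 33.3% of allocations (about 33 of 100) are certain and 70.8% can be guessed. Both figures are exact, given that the size is constant and that someone knows it and tracks assignments. The second condition is feasible in one centre where staff are told each arm, but the article does not show that it was met. It therefore supports a risk of selection, not a finding that selection occurred, and it gives no basis for a single estimate of the bias. A change made at November 2017 could protect only the remaining 100 − 75 = 25 planned allocations and any replacements.

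**What to change.** 1. For every allocation still to be made, replacements included, use a new computer-generated list with randomly varying block sizes, for example 4, 6 and 8. Certain allocations fall from 33% to about 2%.
2. Keep the sizes out of every document that recruiting staff see until recruitment closes. This matters because varying the sizes lowers best-guess success only to about 68% when they are known. It is not a complete cure, since a running tally alone still helps a guesser.
3. For patients already randomised, reconstruct the allocation order and compare baseline EQ-5D-5L and EuroScore across three groups: ministernotomy foreseen, full sternotomy foreseen, not predictable. Do not pool the two foreseen groups, because steering towards opposite arms would cancel. Report it as descriptive: with about 25 forced allocations among 75, a null result is weak reassurance.

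Cost: a new list and an ethics notification, for which the article already provides review of protocol changes. Final arm sizes may be slightly unequal; a block of 8 cut short can leave a difference of at most 4. The baseline comparison needs no new data and can still be done if recruitment has closed.
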